### Statistical analysis

Baseline data and participant attributes, average drinking amount on drinking days, AUDIT-C and AUDIT scores, and response at each scale of secondary outcome measures at each measurement point will be analyzed by a descriptive statistic.

Furthermore, baseline data, attributes, and changes in the average daily drinking amount (1 drink = 10 g of pure alcohol) before and after intervention are compared with the differences between the two groups. We will also compare the measurement points within the groups and compare the groups in terms of genotypes. For these analyses, we use the *t*-test, paired *t*-test, Wilcoxon rank-sum, chi-square, Mann–Whitney *U*, and Kruskal–Wallis tests as appropriate. The selection of the analysis method depends on the parametric and nonparametric data obtained from the results of descriptive statistics and normality tests to determine. In addition, the change in the average amount of drinking (1 drink = pure alcohol 10 g) in each group is examined by calculating the effect size. Data will be analyzed using IBM SPSS Statistics for Windows version 28. If the intervention is not possible in the intervention group, or if no response will be obtained after 1 month in the control group, it will be excluded from the analysis.

Regarding qualitative data (positive aspects about the alcohol constitution test, reasons, etc.), we will examine them by using an inductive analysis method with qualitative coding. The code extracted to ensure reliability will be analyzed by multiple researchers, including those with qualitative research experience.

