### Participants

We included students and graduate students, and staff aged 20–30 years at the University of Tsukuba. The average amount of daily or one-occasional drinking is more than 40 g of pure alcohol for males and more than 20 g for females. They provided their consent to participate in this research.

The exclusion criteria are those who did not wish to disclose the results of the alcohol constitution test and those who have difficulty communicating in Japanese. Participation is voluntary, and participants will be withdrawn if they request to stop participating.

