### Primary outcome measures

According to participants’ average amount of daily drinking (g = pure alcohol, 1 drink = 10 g of pure alcohol), we will compare the effects of interventions by adding information on the genotypes of alcohol-metabolizing enzymes to the content of conventional teaching materials.

The questionnaire provides the following examples of the drink conversion table for alcoholic beverages (Sake: 15% alcohol concentration, 180 ml = 2 drinks; beer: 5% alcohol concentration, 500 ml [medium bottle/medium mug or can beer] = 2 drinks; whiskey brandy: 43% alcohol concentration, 60 ml [double] = 2 drinks; shochu: 25% alcohol concentration, 100 ml [cup half ] = 2 drinks; canned shochu: 7% alcohol concentration, 350 ml = 2 drinks; cocktails, fruity taste, etc.: 5% alcohol concentration, 350 ml [canned] = 1.5 drinks, 500 ml [canned] = 2 drinks; wine: 12% alcohol concentration, 150 ml (glass ) = 1.5 drinks; plum wine: 12% alcohol concentration, 90 ml [small glass] = 1 drink). We ask the answer of the average number of drinks on the drinking day of the past month.

A similar example is shown in the drinking calendar, and the drinking contents (alcohol type and alcohol concentration) and amount on the day of drinking will be recorded for half a year. From the record of the calendar, the sum of the drinking amount (pure alcohol amount) and the number of drinks is calculated using the following generally accepted formula: amount of liquor (ml) × degrees or %/100 × 0.8 (specific gravity) = pure alcohol content (g).

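### Change in drinking is compared unadjusted, with a test chosen from the trial data; the planned within-arm tests and effect sizes cannot show efficacy, and no paired rank test is listed

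*Protocol article*

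**What the plan says.** The Primary outcome measures section defines the outcome: "According to participants’ average amount of daily drinking", in grams of pure alcohol, with the two teaching approaches to be compared on it. The Statistical analysis section then fixes four things.

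- **Between-arm comparison.** Baseline data, attributes and changes in average daily drinking "before and after intervention are compared with the differences between the two groups". No covariate is named. The tests listed are the t-test, paired t-test, "Wilcoxon rank-sum, chi-square", Mann-Whitney U and Kruskal-Wallis.
- **Choice of test.** "The selection of the analysis method depends on the parametric and nonparametric data", as judged from descriptive statistics and normality tests.
- **Within-arm comparison.** "We will also compare the measurement points within the groups and compare the groups in terms of genotypes".
- **Effect size.** The change in average drinking "in each group is examined by calculating the effect size".

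The Participants section admits people whose average daily or per-occasion drinking is "more than 40 g of pure alcohol for males and more than 20 g for females". The Randomization section describes simple randomisation, 100 per arm, with no stratification.

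**The concern.** The section names no single primary analysis. A t-test compares means and a rank test compares distributions, so choosing between them from the data also leaves open which quantity is estimated. The baseline amount is collected but none of the listed tests can use it as a covariate.

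Participants are admitted on a variable very close to the outcome. Part of a high baseline value is temporary, so the group mean should drift down at follow-up in both arms. A paired test or an effect size computed inside one arm counts that drift as change. If such results are reported beside the randomised comparison, they can be misread as a benefit of the genotype session, of the handbook, or of both.

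The test list also leaves the within-arm comparison without a valid rank test. Rank-sum and Mann-Whitney U are two names for one independent-samples test, and the only paired test listed is the t-test.

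**Working it through.** **Inputs.** From the article: 100 per arm, total 199 rounded to 200, effect size 0.2, alpha 0.05, power 0.8 (Sample size). Not in the article and therefore assumed: two-sided testing, the baseline-to-follow-up correlation r (range 0.3 to 0.8), and the share of drinkers above the entry threshold (30%).

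**1. The plan's own figure.** A two-group F test with f = 0.2, equivalent to a standardised difference of 0.4, has power 0.7997 at 198 and 0.8017 at 199, so 199 is reproduced. A paired t-test with d = 0.2 also gives 199. The article does not say which was meant. I use 0.4 SD below because that is the two-group reading.

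**2. Fall expected in each arm with no effect.** For the top 30% of a standard normal, the cut is z = 0.524, the mean is 1.159 and the variance is 1 + 0.524 × 1.159 − 1.159² = 0.26. With r = 0.6:
- expected fall = (1 − r) × mean = 0.4 × 1.159 = 0.46 SD
- variance of change = (1 − r)² × 0.2645 + (1 − r²) = 0.042 + 0.640 = 0.682
- within-arm standardised change = 0.464 / √0.682 = 0.56

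A simulation with no effect (3000 runs, 100 per arm, entry above 0.5 SD) gave a significant within-arm paired test in 100%, 100% and 97% of trials for r = 0.4, 0.6 and 0.8.

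**3. The randomised comparison in the same simulation.** The between-arm change-score test rejected in 5.3%, 5.0% and 5.0% of trials, and ANCOVA in 5.1%, 4.7% and 5.0%. Neither is biased on average. Per 1 SD of baseline difference between arms, the change-score contrast moved by −0.60, −0.41 and −0.22 SD, and the ANCOVA estimate by 0.00, −0.01 and −0.02 SD.

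To scale this: with top-30% entry the standard error of the baseline difference is √(2 × 0.2645 / 100) = 0.073 SD. A two-standard-error imbalance (0.145 SD) at r = 0.6 would move the change-score contrast by about 0.4 × 0.145 = 0.06 SD.

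**4. Precision.** In units of the unselected SD, the variance per person is:
- ANCOVA: 1 − r²
- change score, no selection: 2(1 − r)
- change score, top-30% entry: (1 − r)² × 0.2645 + (1 − r²)

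Power is from the noncentral t with noncentrality 0.4 / √(2V/100).

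| r | V: ANCOVA | V: change, top 30% | V: change, no selection | Relative efficiency (top 30% / none) | Power: change, top 30% | Power: change, none | Power: ANCOVA |
|---|---|---|---|---|---|---|---|
| 0.3 | 0.91 | 1.040 | 1.40 | 1.14 / 1.54 | 79% | 66% | 84% |
| 0.5 | 0.75 | 0.816 | 1.00 | 1.09 / 1.33 | 88% | 80% | 90% |
| 0.7 | 0.51 | 0.534 | 0.60 | 1.05 / 1.18 | 97% | 95% | 98% |

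**5. Data-driven choice of test.** Under no difference, choosing between t-test and Mann-Whitney after a normality test gave a type I error of about 4.5% (normal and skewed data). Taking the smaller of the two p-values gave 5.4% (normal) and 6.1% (skewed).

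**The case against.** Several points on the other side have force.

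- A reader might infer that regression to the mean biases the between-arm comparison of change. It does not: randomised arms regress equally on average, and step 3 shows type I error near 5%. The misreading is confined to the within-arm results, apart from chance imbalance.
- A reader might quote the no-selection figures as the gain from ANCOVA (18 points of power at r = 0.3). That would combine an untruncated baseline with an entry rule that truncates it. Under top-30% entry the gain is about 5, 3 and 1 points.
- A reader might infer that the normality pre-test inflates error materially. The simulation does not support this. The fault is that test and estimand are not fixed.
- Nothing in the article says that a within-arm result will be offered as evidence of efficacy; these comparisons are introduced as additional.
- Covariate lists are often left to a fuller document, and one exists here (Data Availability). The absence of a list alone is no fault. What stands is that the article does state a menu of tests, none able to adjust, and a data-driven rule for choosing among them.
- A change score already removes stable sex differences in level, and no loss from omitting sex has been quantified. Sex belongs in the model because the entry threshold differs twofold by sex, not because a loss has been shown.
- Listing rank-sum next to Mann-Whitney U is plausibly a slip for signed-rank. If rank-sum really were run on paired data, power would be about 37% against 68% (r = 0.5, shift 0.25 SD, assumed). As it stands this is a wording correction.

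**Conclusion.** The point holds in limited form. The stated analysis is unadjusted, its test is not fixed in advance, and its within-arm tests and per-arm effect sizes would very probably look favourable in both arms without any effect. The between-arm comparison of change is valid on average, but it is exposed to chance baseline imbalance that simple randomisation permits and that ANCOVA removes.

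The gain in precision is modest if entry truncates baseline strongly and larger if it does not. It rests on an unstated correlation, an assumed 30% selection, normal data and a linear relation with equal underlying variances at baseline and follow-up. ANCOVA is the more precise method for every r below 1, so the direction does not depend on these assumptions. This is worth correcting, but it does not invalidate the trial.

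**What to change.** By a dated amendment:

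- Name one primary between-arm analysis at one time point, for example 6 months: a linear model of the follow-up amount on arm, baseline amount and sex, with robust standard errors and a 95% confidence interval.
- Drop the normality test as a rule for choosing the analysis.
- Report the between-arm effect size in place of one for each arm.
- Present within-arm changes descriptively, without p-values.
- Replace Wilcoxon rank-sum with Wilcoxon signed-rank for any paired rank comparison.

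The baseline amount and sex are already collected, so no participant procedure changes; the work is wording and analysis code. The Background and Monitoring sections say that some analysis is under way and that intermediate results are shared at monthly meetings. The amendment should therefore state what had been seen when it was made.

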### Sample size

With reference to previous studies [13, 22], the total sample size was 199, calculated with a power size of 0.2, an *α* error of 0.05, and a power of 0.8 using the power analysis software (G * Power3) [24]. In total, we include 200 participants (100 in the intervention group and 100 in the control group).

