## Monitoring

Although this study is an intervention study, it is an educational intervention, and saliva testing is not considered invasive. Therefore, there is no data monitoring. To maintain compliance, we collaborate with researchers to attend monthly online meetings to share progress, data collection, and intermediate analysis results and discuss issues. Regarding the decision to suspend the recruitment of participants, the progress of the trial will be shared at the meeting, and if there is no problem in conducting the exam, the recruitment will be suspended when the number of subjects to be analyzed reaches the target. This research is subject to progress checks and audits every 6 months by the Institutional Review Board, and the person in charge of the audit is independent of this study.

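### Randomised participants are excluded from the analysis by a different post-randomisation rule in each arm, and recruitment replaces them, so the analysed groups lose the protection of randomisation

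*Protocol article*

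**What the plan says.** All references are to the protocol article.

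- **Exclusion rule** (Statistical analysis): a participant is dropped under the condition "If the intervention is not possible in the intervention group, or if no response will be obtained after 1 month in the control group". Delivery of the session decides in the intervention arm, and questionnaire response in the control arm.
- **Recruitment** (Monitoring): "the recruitment will be suspended when the number of subjects to be analyzed reaches the target".
- **Target** (Sample size): "the total sample size was 199", rounded up to 200, or 100 per arm. No allowance for loss is mentioned. The Randomization section describes a list marked before recruitment, also with 100 per group.
- **Timing**: the genotype report is mailed to intervention participants about a month after saliva collection, and the session follows it (Abstract; genotype testing and results report).
- **Follow-up**: the intervention arm is surveyed 1 month after the session and at 3 and 6 months from baseline, the control arm at 1, 3 and 6 months from baseline (Abstract; Measures).
- **Blinding**: open-label, with participants knowing their arm when they consent (Overview of the study design; Discussion).

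The article nowhere describes an analysis of all participants as randomised. It does not present the exclusion rule as defining a secondary, per-protocol set.

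**The concern.** Randomisation makes the two groups comparable at allocation. A rule that removes people for what happens afterwards keeps that comparability only if it selects the same kind of person in both arms. These rules do not measure the same thing. One is about receiving treatment, the other about returning a form.

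Whether someone attends a session about their drinking, after a genotype result has arrived by post, can depend on the arm, on the result and on willingness to change. The protocol treats readiness to change as relevant, since stage of change is a secondary outcome. If those removed would have changed their drinking differently from those kept, the primary comparison carries a bias that more recruits cannot remove.

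**Working it through.** **1. Set the two rules side by side.**

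| | Intervention arm | Control arm |
|---|---|---|
| Trigger for exclusion | Session not delivered | No 1-month response |
| Nature of trigger | Treatment receipt | Outcome response |
| As written, dropped despite 3- and 6-month data? | Yes, if the session did not take place | Yes, if only the early form is missing |
| Equivalent rule in the other arm? | None stated | None stated |

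The control rule might instead mean no reply once the month of reminders in Measures has run out. It would still be a response rule, so the asymmetry remains.

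**2. Reproduce the plan's own figure.** The inputs are an effect size of 0.2, alpha 0.05 and power 0.8. A total of 199 is obtained for a paired or one-sample t-test with d = 0.2 (two-sided), or for a two-group F-test with Cohen's f = 0.2, that is d = 0.4. A two-sample t-test with d = 0.2 would need 788. So 199 is reproducible and this point does not rest on a wrong sample size, but the meaning of 0.2 is not settled.

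**3. Formula for the bias.** Let q be the share of an arm excluded and g the gap in mean outcome, in SD, between excluded and retained. Dropping the excluded shifts that arm's mean by q × g. The bias in the comparison is

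(q × g) intervention − (q × g) control.

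**4. Put in assumed values.** The documents give neither q nor g, so every value here is an assumption. Because excluded participants are replaced, 100 v 100 are analysed. With no true effect, the rejection rate of a two-sided 5% t-test comes from the noncentral t with 198 df and noncentrality bias × √(100 × 100 / 200) = bias × 7.07.

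| Intervention q, g | Control q, g | Bias (SD) | Type I error |
|---|---|---|---|
| 10%, 0.3 | no bias | 0.10 × 0.3 = 0.03 | 5.5% |
| 15%, 0.5 | no bias | 0.15 × 0.5 = 0.075 | 8.2% |
| 30%, 0.5 | no bias | 0.30 × 0.5 = 0.15 | 18.4% |
| 15%, 0.5 | 10%, 0.5 | 0.075 − 0.050 = 0.025 | 5.4% |

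**5. Effect of replacement.** Neither q nor g changes when further recruits pass through the same filters. Replacement restores the analysed number and leaves the bias as it was. It also needs allocations beyond the 100-per-group list, and the article does not describe how that list would be extended.

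**6. Cost of closing at 200 randomised.** Take d = 0.4 and an assumed 15% loss, leaving 85 per arm. The noncentrality is 0.4 × √42.5 = 2.61 and power is about 74%, against about 80% with 100 per arm. To keep 200 analysable, randomise 200/(1 − loss): 223 at 10%, 236 at 15%, 250 at 20%.

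**The case against.** The best defence is that both rules are ordinary handling of dropout. Controls who do not answer at 1 month may also be the less engaged, so the two filters could largely cancel. The last scenario shows this: the bias falls to 0.025 SD and the type I error is close to nominal. That stands, and it is why the bias must be stated as a difference between arms. But nothing in the plan makes the filters match, and nothing limits how many may be excluded.

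Other parts of the defence also stand:

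- The session is about 30 minutes as a guide, can be held online, and saliva can be collected by mailed kit. The hurdle is modest, and some sessions may fail for logistical reasons unrelated to drinking.
- The analysis compares changes in drinking. A difference in drinking level between excluded and retained need not be a difference in change.
- Nothing says exclusions will go unreported. A reader might infer that replacement conceals attrition, but the article does not support that.

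The defence that a statistical analysis plan may specify an as-randomised analysis does not help. It would contradict a rule the article states, and the two would have to be reconciled.

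**Conclusion.** The point holds. Followed as written, the plan compares groups selected after allocation by unlike criteria, in an open-label trial, for the primary outcome. The size is unknown. Under the assumed values above, the bias runs from 0.025 to 0.15 SD and the type I error from about 5.4% to 18.4%. These figures show what is possible, not what is expected.

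Three stronger readings are tempting and are not supported:

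- **The trial is no longer randomised.** Allocation follows a pre-marked list and stays random, and recruiting to an analysed number does not break it. Only the analysed comparison loses protection.
- **The bias favours the intervention.** This is plausible if non-attenders are less willing to change, but no figure in the documents establishes it.
- **The bias is a fixed share of the planned effect.** For example, 0.075 SD is about 38% of the effect if 0.2 is Cohen's d, but about 19% if it is Cohen's f (d = 0.4). The article says only "calculated with a power size of 0.2".

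Because the rule governs the primary comparison and is cheap to change, it should be corrected before analysis.

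**What to change.** Replace the exclusion sentence in Statistical analysis with text to this effect:

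*All randomised participants are analysed in the arm to which they were assigned, using all available responses (for example, a mixed model for repeated measures at the 3- and 6-month points, timed from baseline in both arms). Intervention participants who do not take the test or the session continue to receive the scheduled questionnaires.*

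In addition:

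- For intervention participants without a session, define the first follow-up from baseline, since they have no session date to count from.
- Keep the present exclusion rule only as a labelled per-protocol sensitivity analysis, and report exclusions by arm.
- In Monitoring, tie the end of recruitment to a number randomised that is fixed in advance. If it stays at 200, restate the power with an allowance for expected loss. If 200 analysable participants are wanted, raise the number randomised as shown in the working.

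The cost is a change of wording, a few follow-up e-mails, and some dilution of the estimate by non-attenders. The 3- and 6-month surveys of the intervention arm are already scheduled. There is also either some loss of power at 200 randomised or additional recruitment to avoid it.

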## Alcohol-metabolizing enzyme genotype testing and results report

Briefly, the intervention group will read the instructions for the alcohol-metabolizing enzyme test, sign the consent form, undergo saliva collection using a sponge swab from the test kit, and receive a report of the results approximately after 1 month. The inspection contractor will mail the result report to the participants. If face-to-face explanation and inspection are difficult to conduct, the test kit will be mailed to the participants.

In the control group, testing will be conducted on those who wish to be tested after 6 months from baseline. After receiving the test results, their requests will be confirmed, and the intervention will be performed.

Regarding the report of the results of the alcohol-metabolizing enzyme test, we have created a pamphlet that includes contents common to each of the five types of constitutions and the contents for each constitution. The main contents are as follows:Participants’ alcohol constitution (what type of constitution from A to E, characteristics by constitution type)Mechanism of alcohol decomposition, function of metabolic enzymes, and constitution by combinationRisks of diseases associated with drinking by alcohol constitution (every five types) and points to remember (comments by the constitution)How to interact with and drink alcohol that suits participants’ alcohol constitution, and how to absorb alcohol ingenuity in nutrition and eating and drinking to help slow down the metabolismDrinking habit screening test (AUDIT-C)Appropriate drinking and liver rest days, proper drinking method, alcohol calorie, and metabolism, obesity, etc.Inappropriate drinking: drinking while pregnant/lactating, drunk driving, alcohol harassment, and habitual use/heavy drinking

## Intervention training and intervention

### Intervention training

The intervening researcher is a nurse who had experienced caring for patients with health problems resulting from excessive drinking and who trained in intervention by physicians providing treatment to reduce drinking at the university. Specifically, this nurse will conduct simulated interventions with physicians online and face-to-face, receive advice (approx. 2 h), and observe physician’s interventions in outpatients (approx. 20 people).

